### Outcomes

#### Primary outcome

Comparative predictive ability of prognostic models incorporating MRE severity scores (MEGS, sMaRIA and Lémann index) versus models using standard characteristics alone to predict disabling CD (modified Beaugerie definition) within 5 years of new diagnosis.

#### Secondary outcomes

Comparative predictive ability of prognostic models incorporating MRE severity scores (MEGS, sMaRIA and Lémann index) versus models using standard characteristics alone to predict the development of Montreal B2 / B3 disease or Liège severe disease at 5 year follow-up.Identification of the best combination of individual MRE features to predict disabling CD within 5 years of new diagnosis.Average per-patient and national healthcare costs incurred within 5 years of new diagnosis.Patient, disease phenotype and imaging characteristics associated with higher economic costs within 5 years of diagnosis.

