#### Additional retrospective cohort: inclusion criteria

The retrospective cohort will be added to METRIC accruals to achieve the required sample size.

Inclusion criteria for the retrospective cohort are as follows:

Patients aged 16 years or more with newly diagnosed CD, based on endoscopic, histological, clinical and radiological findings.MRE acquired according to METRIC standard minimum sequence data set, and performed either <3 months before or after diagnosis.Normal institutional practice is to perform MRE in all new diagnoses of CD.At least 4 years clinical follow-up data available.

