##### Lémann Index (LI)

The LI^34^ (table 4) is based on comprehensive assessment of structural bowel damage, including stricturing, penetrating lesions (ﬁstulae and abscesses) and surgical resection, and is applicable to different settings, such as early or advanced disease, patients with or without surgery, or with different CD locations and extension. The score comprises several factors that can be assessed either clinically, or using imaging or via endoscopy. We will use the imaging-derived score. Since the anal canal will not have been imaged specifically for METRIC, we will omit this score.

**Table 4 T4:** Derivation of the Lémann Index

Organ	Method of assessment	N*	Segment	Grade 1	Grade 2	Grade 3
Surgical interventions†						
Upper tract	History	3	Oesophagus, stomach, duodenum	–	Bypass diversion or stricturoplasty	Resection
Small bowel	History	20	Each 20 cm SB segment	–	Bypass diversion or stricturoplasty	Resection
Colon/rectum	History	6	Each colonic segment	–	Stoma, bypass diversion or stricturoplasty	Resection
Stricturing lesions						
Upper tract	MRI	2	Stomach, duodenum	Wall <3 mm; segmental enhancement without prestenotic dilatation	Wall thickening ≥3 mm or mural stratification with no prestenotic dilatation	Stricture with prestenotic dilatation
Small bowel	MRI	20	Each 20 cm SB segment	Wall <3 mm; segmental enhancement without prestenotic dilatation	Wall thickening ≥3 mm or mural stratification with no prestenotic dilatation	Stricture with prestenotic dilatation
Colon/rectum	MRI	6	Each colonic segment	Wall <3 mm; segmental enhancement without prestenotic dilatation	Wall thickening ≥3 mm or mural stratification with no prestenotic dilatation	Stricture with prestenotic dilatation or >50% of the lumen
Penetrating lesions						
Upper tract	MRI	2	Stomach, duodenum	–	Deep transmural ulceration	Phlegmon or fistula
Small bowel	MRI	20	Each 20 cm SB segment	–	Deep transmural ulceration	Phlegmon or fistula
Colon/rectum	MRI	6	Each colonic segment	–	Transmural ulceration	Phlegmon or fistula

*n is the number of segments within a particular organ.

†This information will be collated from the original METRIC records, although a relevant surgical history will be very rare since included patients are, by definition, those with a new diagnosis of Crohn’s disease.

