#### Primary definition of disabling disease

The primary definition of disabling disease will be a modified version of that described by Beaugerie *et al*.^38^ The original definition has been modified to clarify some of the symptoms and to permit the use of disease-modifying therapy, since this has become a common preventative measure in modern practice. Disabling disease will therefore be defined as any of the following:

Hospitalisation after CD diagnosis for flare or disease complication, as judged by the treating clinician.More than two corticosteroid courses required over 5 years and/or dependence on corticosteroids.Any intestinal resection >50 cm, or surgical operation for perianal disease (examination under anaesthesia without seton placement does not meet this criterion; abscess drainage and/or seton placement does).Chronic disabling symptoms, defined as a cumulative time of over 12 months of one or more of the following:Diarrhoea with nocturnal stool (getting up for a bowel movement after having gone to bed).Urgency (defined as having to rush to the toilet for a bowel movement).Abdominal pain due to intestinal obstruction (requires imaging confirmation or surgical proof).Fever (documented tympanic temperature of >38.0°C or oral temperature of>38.3°C).Fatigue.Joint pain not due to an alternative cause.Uveitis.Pyoderma gangrenosum.

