#### Alternative definitions of disabling disease

Since the Beaugerie criteria are imperfect, further definitions of adverse outcomes will also be collected; specifically the Liège criteria^37^ and Montreal behaviour criteria.^39^

The Liège criteria are met if any of the following occur:

Development of complex perianal disease.Any colonic resection.Two or more SB resections.A single SB resection of >50 cm.Definitive stoma.

Complex perianal disease is defined as per the American Gastroenterological Association,^40^ and the perianal disease modifier will be collected.

The Montreal behaviour criteria classify CD as either inflammatory (B1), stricturing (B2) or penetrating (B3). Stricturing disease will be defined as a fixed luminal narrowing of >50% relative to normal proximal bowel. Penetrating disease will be defined as an intra-abdominal or enterocutaneous fistula, inflammatory mass, or abscess.

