### Statistical methods—outcomes

#### Primary outcome

Comparative predictive ability of prognostic models incorporating MRE severity scores (MEGS, sMaRIA and Lémann index) versus models using standard characteristics alone to predict disabling CD (modified Beaugerie definition) within 5 years of new diagnosis

We will develop a multivariable prognostic model using prespecified standard predictors (age at recruitment as new diagnosis, smoking, gender, disease status at diagnosis (stricturing disease, perianal disease, severe endoscopic disease, location of disease as L1/L2/L3/L4, initial need for steroid therapy, weight loss of at least 5 kg, CRP, white cell count, faecal calprotectin, haemoglobin and platelets). Continuous variables will be retained where possible, with transformations and polynomial transformations when needed. Categorised variables will be retained as prespecified in clinical report form except where modelling requires combination of categories with small numbers. Missing covariates will be handled via multiple imputation, under the ‘missing at random’ assumption.^44^ We will compare the additive effect on model fit of each MRI score (MEGS, sMaRIA and LI as PCA variables) to the baseline standard model as a linear offset. An increase in model performance will be based on an improvement in the number of patients correctly classified for disabling disease, using models including MRE compared with a standard model. Model performance will be measured using sensitivity, specificity and net benefit. We will also assess difference in model fit using Bayesian Information Criteria (BIC) and we will report c-index for each model. Internal validation using bootstrap samples (sampling with replacement) will use at least 200 or more bootstrap samples until estimates remain stable. Model prediction at 1-year, 2-year and 3-year time horizons will also be reported.

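### Events count from diagnosis although the MRE may follow by up to 3 months, and the Montreal B2/B3 outcome is not restricted to patients who are B1 at baseline

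*Protocol article*

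**What the plan says.** **Primary endpoint.** The Primary outcome section sets the prediction window at 5 years from new diagnosis. Under Primary definition of disabling disease, one sufficient criterion is "Hospitalisation after CD diagnosis for flare or disease complication, as judged by the treating clinician". In the retrospective cohort the MRE may be "performed either <3 months before or after diagnosis". In the METRIC cohort, diagnosis may precede recruitment by up to 3 months, so there too the scan can follow diagnosis. No rule is given for an event dated between diagnosis and scan.

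**Montreal endpoint.** The Secondary outcomes section describes models "to predict the development of Montreal B2 / B3 disease or Liège severe disease at 5 year follow-up". The definitions, under Alternative definitions of disabling disease, are of a state: "Stricturing disease will be defined as a fixed luminal narrowing of >50% relative to normal proximal bowel" and "Penetrating disease will be defined as an intra-abdominal or enterocutaneous fistula, inflammatory mass, or abscess". Neither has to be new since diagnosis or since the scan.

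The inclusion and exclusion criteria remove nobody for being B2 or B3 at entry. The standard predictors under Statistical methods include "disease status at diagnosis (stricturing disease, perianal disease, severe endoscopic disease", so patients with stricturing disease at baseline are expected. Secondary outcome 1 is to be modelled in the same way as the primary, with no added restriction on who is at risk.

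**Overlap with the MRE scores.** The Lémann Index is described as a "comprehensive assessment of structural bowel damage, including stricturing, penetrating lesions". Table 2 adds points to MEGS for abscess and for fistula. Both are scored on the baseline scan.

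**The concern.** A prognostic model should use information available at time zero to predict what happens afterwards. Here two things can break that order.

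First, in a patient diagnosed in month 0, admitted in month 1 and scanned in month 2, the scan is credited with predicting an admission that has already happened, and that may have prompted it.

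Second, a patient with an abscess on the diagnostic MRE scores on MEGS and meets B3 on the same day. That is detection of existing disease. The purpose set out in the Introduction is to identify patients for early therapy so as to prevent future complications, and a model that partly recognises complications already present does not speak to that.

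**Working it through.** **1. The plan's own counts reproduce.** From the Assumptions section, N = 207 and the 5-year prevalence of disabling disease is 55% to 60%.
- Events: 207 × 0.55 = 113.9 and 207 × 0.60 = 124.2, matching 114–124.
- Non-events: 207 × 0.40 = 82.8 and 207 × 0.45 = 93.2, matching 83–93.
- Audit: 5/33 = 15.2%; × 12/11.3 = 16.1% at 1 year; 1 − (1 − 0.161)^5 = 58.4% at 5 years, matching 58%.

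The point does not dispute these figures. The plan states linear development, but its 58% comes from compounding, so both forms are used below.

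**2. Primary events that could precede the scan.** Let p be the 5-year prevalence and m the lag in months from diagnosis to MRE, taken as the same for everyone.
- Constant hazard: 207 × [1 − (1 − p)^(m/60)].
- Linear accrual: 207 × p × m/60.

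| Lag | Constant hazard, p = 0.55 to 0.60 | Linear, p = 0.55 to 0.60 |
|---|---|---|
| 1 month | 2.7 to 3.1 | 1.9 to 2.1 |
| 2 months | 5.4 to 6.2 | 3.8 to 4.1 |
| 3 months | 8.1 to 9.3 | 5.7 to 6.2 |

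At 3 months the share of all events is 3/60 = 5% under linear accrual. Under constant hazard it is 8.1/113.9 = 7.1% to 9.3/124.2 = 7.5%. The 3-month row is an upper bound on timing, because the retrospective cohort also admits scans before diagnosis, where the problem does not arise.

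**3. Montreal: which lesions sit on both sides.**

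| Finding at baseline | Outcome | Standard model | Lémann Index | MEGS | sMaRIA |
|---|---|---|---|---|---|
| Stricture | B2 | yes | yes | no item | no item |
| Intra-abdominal or enterocutaneous fistula, mass or abscess | B3 | not listed | yes | abscess, fistula | no item |

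A prevalent stricture recorded in the baseline variable helps both models, so it adds little to the difference between them. Prevalent penetrating disease is captured directly only by the MRE scores, because perianal disease, which is in the standard model, is not part of the stated B3 definition. Strictures that the baseline variable misses also favour MRE.

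**4. Montreal: how many patients.** The document gives no baseline prevalence of B2/B3. Assuming 5% to 30%, 207 × 0.05 = 10 to 207 × 0.30 = 62 patients would meet the outcome on day 0. If 20% of the rest then progress (also assumed), the prevalent share of all B2/B3 outcomes runs from 10.4/(10.4 + 39.3) = 21% to 62.1/(62.1 + 29.0) = 68%. This illustrates how far the risk set matters. It does not estimate the gain credited to MRE.

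**The case against.** **The document never says that prevalent B2/B3 is counted.** The secondary outcome speaks of development, and the consensus panels record the date on which the endpoint was met, which would separate old from new disease. Incident disease was probably meant. That stands, and it makes the Montreal part softer than the primary part. But no rule uses the date, and the written definitions, eligibility and modelling instruction together give a risk set that includes prevalent cases.

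**A reader might infer that a large false gain for MRE can be shown.** With 20% prevalent and 20% to 30% of the rest progressing (both assumed), a score that detects every prevalent case and predicts nothing else has a c-index of 0.2/0.36 + 0.5 × 0.16/0.36 = 0.78, or 0.2/0.44 + 0.5 × 0.24/0.44 = 0.73. That is the c-index of the score alone. The stated outcome is the improvement over a standard model that already includes stricturing disease, and these figures do not measure it.

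**A reader might also infer that score and outcome are one observation.** They overlap only in part. MEGS has no stricture item, sMaRIA has none of the three features, and the Lémann Index grades small-bowel strictures by prestenotic dilatation whereas B2 uses narrowing above 50%.

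**The primary effect is small.** This stands. Some criteria (more than two steroid courses, over 12 months of symptoms) could hardly be met within 3 months, so applying the whole composite's rate to that period is rough. Early admissions might instead cluster near diagnosis, but no figure is given. Blinded reading keeps knowledge of an admission out of the score but does not restore the time order.

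**Conclusion.** The point holds in two parts of different strength.

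The primary part follows from stated rules: the clock starts at diagnosis and the scan can come later. Its size is modest. At the plan's event rate it is at most about 6 to 9 of 207 patients if every MRE were at 3 months, and about 2 to 3 at a 1-month lag. This assumes that early events occur at the average rate. The direction is not established: a flare still visible on the scan would favour MRE, and treatment given before the scan could work the other way.

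The Montreal part is an at-risk set that does not match the promised outcome. Bias towards MRE is likely, mainly through prevalent penetrating disease and strictures that the baseline variable misses. Its size depends on baseline B2/B3 prevalence and on how completely the stricturing variable is recorded, and the document gives neither. It affects a secondary outcome whose models are fitted only if events are adequate.

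Liège raises the same question through complex perianal disease, but that endpoint is descriptive by default (about 41 events expected).

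**What to change.** - **Primary endpoint:** set time zero at the later of diagnosis and MRE date and count only events after it. State how patients with an earlier event are handled and report their number. Keep the from-diagnosis analysis as sensitivity.
- **Montreal endpoint:** fit the models only in patients who are B1 at baseline, with B2/B3 first documented after the baseline MRE as the event. Report prevalent B2/B3 descriptively.
- **Liège endpoint:** apply the same rule only if it is modelled, excluding patients with complex perianal disease at baseline.

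The cost is wording in the analysis plan. The panels already record endpoint dates, and diagnosis and MRE dates are needed to apply the eligibility window. The downside is fewer Montreal events, which may leave that endpoint descriptive under the plan's own adequacy condition, and the loss of a few primary events.

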### Assumptions

We assume the prevalence of our modified Beaugerie definition of disabling disease will be approximately 55%–60%; this is informed primarily by the external validation cohort^37^ of the Beaugerie descriptors, in which 57% of 361 participants had developed disabling disease by 5 years. In support, a local audit of 33 newly diagnosed patients at one METRIC recruitment centre found 5 of 33 (15%) patients met the definition by mean 11.3 months, giving 16% at 1 year. Extrapolation to 5 years gives 58% prevalence, similar to that expected from the literature.^37^ We assume that development of disabling disease is approximately linear over time. Therefore, 207 participants will provide 114–124 events and 83–93 non-events (defined by non progression to disabling disease); the smaller proportion defines the minimum sample size for powering a modelling study, where regression methods are used for development (see section below).

### Sample size and justification

The sample size was based on including 207 participants newly diagnosed with CD. During the study, due to problems obtaining consent for additional follow-up hampered by COVID-19, the original target recruitment was necessarily reduced from 167 to 131 from the METRIC prospective cohort, and so an increased target of 76 participant retrospective cohort recruited from METRIC sites is anticipated. We anticipate this sample size will provide between 114 and 124 events (83–93 non-events). The number of the retrospective cohort will be increased to meet the 207 participant target if recruitment to the METRC cohort is below 131.

#### Adequacy of this number of events/non-events

Calculating sample sizes for prognostic studies suffers from a relative lack of readily applied methods suitable for all study designs, since sample size for development depends on whether the primary aim is to select potential variables for a new model (via univariable significance within a data set), or to evaluate a model where the variables have been prespecified and are therefore fixed. In the present study, the variables are fixed since we are explicit that we will test a small number of MRE scores in the context of a model using fixed clinical (?clinicopathological) variables. Therefore, recommendations for sample sizes relevant to external validation are most appropriate. Accordingly, the literature suggests we require 80–100 events for model evaluation where variables are prespecified and fixed.^41^ This also provides sufficient power to assess whether addition of the three MRE scores enhance prediction, under the widely used ‘rule-of-thumb’ of 10–20 events per variable.^42^ We note that recent methods to calculation external validation sample size did not exist in 2017, when this study was powered.^43^

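### The sample size is justified by an external-validation rule, but the models are developed in the same 207 patients, with about 4 to 7 limiting-group patients per parameter

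*Protocol article*

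**What the plan says.** Under Sample size and justification: "The sample size was based on including 207 participants newly diagnosed with CD". Under Assumptions, a 5-year prevalence of 55–60% leads to the statement that "207 participants will provide 114–124 events and 83–93 non-events", and the article adds that "the smaller proportion defines the minimum sample size for powering a modelling study, where regression methods are used for development".

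The section on adequacy of the number of events then takes another line. Because the MRE scores and clinical variables are chosen in advance, it treats them as fixed and concludes: "Therefore, recommendations for sample sizes relevant to external validation are most appropriate". It takes 80–100 events as the requirement and continues: "This also provides sufficient power to assess whether addition of the three MRE scores enhance prediction", under a rule of thumb of 10–20 events per variable.

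The Primary objective is to develop and internally evaluate a model containing both standard and MRE predictors. The statistical methods for the primary outcome say: "We will develop a multivariable prognostic model using prespecified standard predictors". They list those predictors and allow transformations, polynomial terms and merging of small categories. They add the MRE scores to the baseline model as a linear offset and plan at least 200 bootstrap samples for internal validation. External evaluation is left to a later study (Secondary objectives).

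**The concern.** A sample-size rule for external validation presupposes a finished model, coefficients included, applied to new patients. Here only the list of variables is settled in advance. The intercept, every coefficient and any data-driven transformation are estimated in the same patients in whom performance is judged. The Assumptions section recognises this by tying the limiting count to regression used for development. The adequacy section argues as if development were not happening.

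The primary comparison rests on sensitivity, specificity and net benefit, all of which depend on predicted risks. With few limiting-group patients per parameter, unshrunken risks tend to be too extreme and apparent performance too good. Unless this is corrected equally on both sides, it can distort the comparison of MRE with standard models. The documents do not determine the direction of the distortion. A reader of the adequacy section would not know the risk is there.

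**Working it through.** **The article's own figures.** N = 207 (131 + 76), prevalence 55–60%.
- Events: 207 × 0.55 = 113.9 and 207 × 0.60 = 124.2, so 114–124.
- Non-events: 207 × 0.40 = 82.8 and 207 × 0.45 = 93.2, so 83–93.

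Both ranges reproduce. The limiting count is 83–93.

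**Counting predictors** (statistical methods, primary outcome). Age, smoking, gender, stricturing disease, perianal disease, severe endoscopic disease, location, initial steroid need, weight loss, CRP, white cell count, faecal calprotectin, haemoglobin and platelets make 14 variables. Location has four levels (L1–L4), hence 3 parameters, so there are at least 13 + 3 = 16 parameters. Polynomial terms would raise this. Merging location categories could lower it, but not below 14.

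**Ratio = limiting count / number of terms.**

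| Model | Terms | Non-events per term (83–93) | Events per term (114–124) |
|---|---|---|---|
| Baseline, variables | 14 | 5.9–6.6 | 8.1–8.9 |
| Baseline, parameters | 16 | 5.2–5.8 | 7.1–7.8 |
| Plus one MRE score, variables | 15 | 5.5–6.2 | 7.6–8.3 |
| Plus one MRE score, parameters | 17 | 4.9–5.5 | 6.7–7.3 |
| Plus three MRE scores, variables | 17 | 4.9–5.5 | 6.7–7.3 |
| Plus three MRE scores, parameters | 19 | 4.4–4.9 | 6.0–6.5 |
| Three MRE scores only, baseline held fixed | 3 | 27.7–31.0 | 38.0–41.3 |

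No count that includes the baseline predictors reaches 10, even on the larger group. At 10 per parameter, 83–93 non-events support 83/10 to 93/10, that is 8 or 9 parameters. Only the last row meets 10–20.

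**Illustration of overfitting (not relied on).** The documents give no expected model fit, so a Nagelkerke R² of 0.15–0.30 is assumed here. At 57.5% prevalence the maximum Cox–Snell R² is 0.744, so the Cox–Snell values are 0.112–0.223. With 19 parameters the expected uniform shrinkage factor S depends on what that R² means.
- Read as optimism-adjusted, solving 207 = 19 / [(S − 1) ln(1 − R²/S)] gives S of about 0.57–0.74.
- Read as apparent fit, LR = −207 ln(1 − R²) = 24.5–52.3, and S = 1 − 19/LR = 0.22–0.64.

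Either reading implies appreciable shrinkage, but the size follows from the assumption.

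**The case against.** The strongest defence is that the power sentence concerns only the addition of the MRE scores. They enter over a linear offset, apparently one score at a time. With the baseline predictor held fixed, the increment uses one to three parameters and the ratio is 28–31 for three. This stands for that step. A reader might infer that the 10–20 statement is simply false, or that it could hold only with baseline coefficients imported from outside the study. The text supports neither, because an offset can be computed from a model fitted in the same data. What the defence does not do is make that offset known: it comes from a 14-variable model estimated in these 207 patients, and its overfitting carries into the comparison. Nor does it cover the primary objective, which is to develop the combined model.

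Second, bootstrap validation is planned and can estimate optimism. That is true, but it does not raise the ratio or make an external-validation rule apply.

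Third, the article does not say that the models will be unpenalised. Penalisation, parameter caps and calibration slope may be in an analysis plan that is not shown, so their absence here is not a finding.

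Fourth, the article openly says that newer methods for sizing external validation did not exist in 2017, when the study was powered. That explains the use of rules of thumb, but not the choice of a validation rule for a development study.

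**Conclusion.** The point holds in a limited form. The external-validation rationale does not fit a study that develops its models in these patients, and it conflicts with the Primary objective, the Assumptions section and the statistical methods. On the article's limiting count, the ratio is 5.2–6.6 for the baseline model, 4.9–6.2 with one MRE score and 4.4–5.5 with all three. The claim of 10–20 is sound only for the MRE increment conditional on a fixed offset.

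This rests on 14 predictors as listed, location entered with 3 parameters at the lower end of each range, and prevalence of 55–60%. It does not rest on the shrinkage illustration.

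A reader might also infer an arithmetic error or a need for more patients. The event counts are correct. The finding concerns the stated justification and the handling of optimism, and 207 can stand.

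**What to change.** In the adequacy section:
- Remove the argument that external-validation recommendations apply.
- Limit the 10–20 statement to the added MRE terms, conditional on a fixed baseline offset, and say that the offset is estimated in the same patients.
- State that the developed baseline and combined models have about 4–7 limiting-group patients per parameter.

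In the analysis, keep 207 patients. Apply the shrinkage factor from the already planned bootstrap, or penalised fitting, to both the standard and the MRE models. Sensitivity, specificity and net benefit are then compared on optimism-corrected risks. The bootstrap should repeat the baseline fitting, including any choice of transformation, so that optimism in the offset is captured. If the analysis plan already does this, a cross-reference is enough.

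The cost is a less favourable adequacy statement and a little more analysis work. No extra patients or data are needed.
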